## Abstract

**Background:**

Patients with symptomatic internal carotid artery (ICA) or middle cerebral artery (MCA) occlusion with haemodynamic insufficiency are at high risk for recurrent stroke when treated medically.

**Methods:**

The Carotid or Middle cerebral artery Occlusion Surgery Study (CMOSS) trial is an ongoing, government-funded, prospective, multicentre, randomised controlled trial. The CMOSS will recruit 330 patients with symptomatic ICA or MCA occlusion (parallel design, 1:1 allocation ratio) and haemodynamic insufficiency. Participants will be allocated to best medical treatment alone or best medicine plus extracranial-intracranial (EC-IC) bypass surgery. The primary outcome events are all strokes or deaths occurring between randomisation and 30 days post operation or post randomisation and ipsilateral ischaemic stroke within 2 years. Recruitment will be finished by December 2016. All the patients will be followed for at least 2 years. The trial is scheduled to complete in 2019.

**Discussion:**

The CMOSS will test the hypothesis that EC-IC bypass surgery plus best medical therapy reduces subsequent ipsilateral ischaemic stroke in patients with symptomatic ICA or MCA occlusion and haemodynamic cerebral ischaemia. This manuscript outlines the rationale and the design of the study. CMOSS will allow for more critical reappraisal of the EC-IC bypass for selected patients in China.

**Trial registration:**

NCT01758614 with ClinicalTrials.gov. Registered on 24 December 2012.

## Background

Patients with symptoms of cerebral ischaemia associated with ipsilateral internal carotid artery (ICA) occlusion have an annual risk of 5–8% of recurrent ischemic stroke [1, 2]; patients with symptomatic middle cerebral artery (MCA) disease (including severe stenosis and occlusion) have an overall stroke risk of 12.5% per year (ipsilateral: 9.1%) [3]. The annual risks of recurrent ischaemic stroke in patients with symptomatic ICA or MCA occlusion have not obviously improved over recent years [4]. The proportion of recurrence with minor disabling consequences was rather high.

### The pathophysiology of carotid and middle cerebral artery occlusion

#### Collateral circulation

Compensation by a collateral circulation is usually considered important in the pathophysiology of cerebrovascular stenosis and occlusion. The Circle of Willis as the primary collaterals provides immediate diversion of cerebral blood flow (CBF) to ischaemic regions. The compensatory capacity of the primary collaterals depends on their vascular calibre and patency. The ophthalmic artery and leptomeningeal vessels constitute secondary collaterals, and also contribute ancillary collateral flow to distal segments of stenotic or occluded major cerebral arteries [5]. In a case of occlusion of the ICA or MCA over a chronic time course, the features of the secondary collaterals are related to the severity of haemodynamic alterations and metabolic and neuroendocrine mechanisms [5].

Patterns of collateral flow in chronic occlusive cerebrovascular disease are different between the ICA and the MCA [6, 7]. In patients with ICA occlusion, possible compensatory blood flow could be from the contralateral ICA via the anterior communicating artery (AComA) or from the vertebrobasilar system via the posterior communicating artery (PcomA). While anatomic studies show that about 1% of subjects have an absent AComA, 10% of subjects have an absent or hypoplastic proximal anterior cerebral artery and 30% of subjects have absence or hypoplasia of one or other PComA [8].

Because the MCA is located in the downstream of the Circle of Willis, the primary collaterals fail to compensate for the loss of blood flow perfusion; only pial or meningeal to pial collaterals are available in patients with MCA occlusion [6, 7]. However, the pial collaterals are not adequate to maintain normal cerebral haemodynamics. Thus, poor collateral development is considered a risk factor for stroke in patients with MCA occlusion [6, 7.]

Additionally, the development of a collateral circulation does not guarantee its function and its function may be related to age, comorbidities and the duration of ischaemia [9]. Haemodynamics is one of the most important factors [7].

#### Cerebral haemodynamics

The haemodynamic stroke is a kind of stroke subtype caused by local or systemic hypoperfusion. Occlusion of the ICA or MCA is the local factor that contributes to impaired haemodynamics although low blood pressure (BP) or volume might also play a systemic role [10]. According to cerebrovascular autoregulatory mechanisms, CBF could remain static during steady-state changes in cerebral perfusion pressures (CPPs) within a wide range by the occurrence of distal vasodilation. Vasomotor reactivity (VMR) or cerebral vasoreactivity (CVR) is used to describe this capability of cerebral resistance arterioles to change their calibre when CPPs decrease. Decreased VMR indicates preexisting vasodilation induced by ICA or MCA occlusion. When distal vasodilation becomes maximal and CPPs continue to decline, the brain tissue increases the oxygen extraction from the blood in order to maintain normal metabolism and function [11]. That is termed ‘misery perfusion’ or stage II haemodynamic compromise [10]. There is increasing evidence that cerebral haemodynamics play an important role in the long-term prognosis of patients with chronic ICA or MCA occlusion. Some investigators report that the annual risk of ipsilateral stroke is 32.7% in ICA occlusion patients with impaired VMR and poor collateral circulation [4]. Derdeyn et al. also demonstrated that in patients with MCA occlusion, the frequency of impaired haemodynamic compromise was high [12]. So patients in these situations might benefit from revascularisation surgery.

### Cerebral haemodynamic evaluation

Cerebral haemodynamic evaluation is the core factor for patients with ICA or MCA occlusion. Quantitative xenon-computed tomography-(CT) can provide exact data of regional CBF and, accompanied with the Diamox challenge test, can determine the VMR/CVR convincingly [13]. Xenon-CT with the Diamox challenge test has been utilised widely in Japan and the USA, while recently the spread of its usage across the world has been slowed down because of the current limitations in access of FDA.

[^15^O]H_2_O positron emission tomography (PET) not only provides quantitative CBF values, but also cerebral metabolism information. As the basis of the Carotid Occlusion Surgery Study (COSS) funded by the NIH (National Institutes of Health), the St. Louis Carotid Occlusion Study (STLCOS) was performed in order to evaluate the cerebral haemodynamics of patients with ICA occlusion systematically using PET [11]. Using a semiquantitative, count-based hemispheric oxygen extraction fraction (OEF) ratio method, STLCOS first identified the normal OEF ratio threshold from normal control subjects. The risk of all strokes was then found to be 6.0 times higher in patients with stage II haemodynamic failure (with increasing OEF) compared to normal OEF, and the risk of ipsilateral stroke was 7.3 times higher. Unfortunately, because different countries have different situations, [^15^O]H_2_O PET is still limited in many countries, especially in developing countries, because access to [^15^O] requires an on-site cyclotron.

With the spread of modern computed tomography (CT) scanners, the CT perfusion (CTP) technique is easily available in most institutes. Remarkable developments have been achieved in perfusion techniques even though measurement variability (precision) is in the range of 15–30% when region of interest (ROI)-based techniques are used [14]. According to the perfusion technique mechanism, several investigations have tried to identify the normal thresholds for interpreting measurements made with this technique. Waaijer et al. [15] identified that the least variability is located in the MCA territory. Calculation of CTP ratios of bilateral hemispheres may eliminate the variations caused by the selection of the arterial input function (AIF) and venous output function (VOF). If the ROIs drawn in bilateral hemispheres are symmetrical, CTP ratios will be helpful to eliminate the resulting measurement variability. The COSS investigators [16] also tried to compare CTP with [^15^O]H_2_O PET in patients with chronic ICA occlusion and found mean transit time (MTT) to be the best parameter, correlating with the count-based PET OEF ratios (slope = 0.124, intercept = 0.676, *R*
^2^ = 0.590, *p* < 0.001). CTP relative CBF (rCBF) compares favorably to PET relative CBF when processed using a dedicated AIF for each territory (*R*
^2^ = 0.796, *p* < 0.001). According to these results, a combination of decreased CBF ratio (symptomatic side/asymptomatic side) and increasing MTT could help to distinguish stage II haemodynamic failure.

## Methods

### Trial design

The Carotid or Middle cerebral artery Occlusion Surgery Study (CMOSS) trial in China is designed to compare the safety and efficacy of EC-IC bypass surgery with medical therapy in patients with symptomatic ICA or MCA occlusion (within 120 days). It is the subproject of the ‘Five-twelfth’ National Science and Technology Support Program funded by the Chinese government and is a randomised controlled trial (RCT) that plans to enroll 330 patients with equal randomisation to surgical and nonsurgical groups. The allocation ratio will be 1:1. The CMOSS trial will be conducted in 15 centres in China.

### Inclusion and exclusion criteria

#### Inclusion criteria

 Age ranging between 18 and 65 years Digital subtraction angiography (DSA) imaging studies demonstrating occlusion of a unilateral ICA or MCA DSA studies demonstrating less than 50% stenosis of any other vessels especially the contralateral ICA, MCA or basilar artery Modified Rankin Scale (mRS) score 0–2 A qualifying transient ischaemic attack (TIA) or ischaemic stroke in the territory of the occluded ICA or MCA must have occurred within the past 12 months The most recent stoke occurred more than 3 weeks previously The neurological deficit must have been stable for more than 1 month No massive cerebral infarction (more than 50% of the MCA territory) demonstrable in a CT or magnetic resonance imaging (MRI) study CTP demonstrates ‘misery perfusion’ (MTT more than 4 s and rCBF (symptomatic side/asymptomatic side) < 0.95)Must be competent to give informed consentMust be legally an adultMust be geographically accessible and reliable for follow-up

#### Exclusion criteria

 Other neurovascular disease (such as cerebral aneurysm or arteriovenous malformation) conditions likely to cause focal cerebral ischaemia Known unstable angina or myocardial infarction within the last 6 months Pregnant or perinatal stage women Coagulopathy Any diseases likely to lead to death within 2 years Past history of EC-IC bypass surgery Any contraindications or allergy to aspirin or clopidogrel Any heart disease likely to cause cerebral ischaemia including prosthetic valve(s), infective endocarditis, atrial fibrillation, sick sinus syndrome, myxoma, and cardiomyopathy with an ejection fraction of less than 25% Allergy to iodine or radiographic contrast mediaSerum creatinine level > 3 mg/dlUncontrolled diabetes mellitus (fasting blood glucose level > 16.7 mmol/l)Uncontrolled hypertension (systolic BP above 180 mmHg, diastolic BP above 110 mmHg)Severe liver dysfunction (alanine transaminase (ALT) and/or aspartate transaminase (AST) more than three times the normal level)Concurrent participation in any other experimental treatment trialAny condition that in the surgeon’s judgment suggests the patient to be an unsuitable surgical candidate

### Intervention and follow-up

After an Informed Consent Form (ICF) has been signed, all the patients will be given best medical treatment including management of risk factors (elevated systolic BP, elevated low-density lipoprotein cholesterol level, diabetes mellitus, smoking, excess weight). Aspirin (100 mg per day) or clopidogrel (75 mg per day) will be prescribed to the patient and they will discontinue the use of any other antithrombotic therapy (specifically, oral anticoagulant agents) until the 30-day follow-up visit. After that, the experienced neurologists caring for the patient will determine the necessity of antithrombotic therapy.

Surgical intervention will be performed within 7 days after randomisation by attending neurosurgeons who have been certified as chief surgeon in at least 15 consecutive previous EC-IC bypass surgeries. Their surgical record of anastomosis graft patency is greater than 95% and the perioperative stroke and death rate is less than 10%. Standard end-to-side anastomosis of the superficial temporal artery (STA) to the M4 segment (MCA) will be utilised. If the STA is unsuitable, the occipital artery may be used.

All the patients will be followed up at the neurological outpatient clinic on four occasions (at 30 days, 6, 12, and 24 months). Scheduled follow-up examinations are summarised in Table 1. If a potential endpoint event occurs, patients will be examined by neurologists within 24 h. If a stroke is suspected, MRI or CT will be performed as soon as possible.

**Table 1 Tab1:** Follow-up schedule

	Baseline	7 days	30 days	6 months	12 months	24 months
Neurological function evaluation						
NIHSS	✓	✓	✓	✓	✓	✓
mRS	✓	✓	✓	✓	✓	✓
BI	✓	✓	✓	✓	✓	✓
Neuro-imaging evaluation						
Brain CT/MRI	✓DWI	✓	✓	✓	✓	✓
Cerebrovascular CTA/MRA					✓	
DSA	✓	✓^a^			✓^b^	✓
CTP	✓	✓^a^		✓	✓	✓
Medication						
Current medication	✓	✓	✓	✓	✓	✓
Medication compliance		✓	✓	✓	✓	✓
Adverse events	✓	✓	✓	✓	✓	✓
Physical examination	✓	✓	✓	✓	✓	✓
Vital signs	✓	✓	✓	✓	✓	✓
Laboratory tests	✓	✓^a^		✓	✓	✓
Pregnancy test	✓					✓
Electrocardiogram	✓					✓
Chest X-ray	✓					✓

^a^Bypass surgical group only; ^b^If necessary; *CT* computed tomography, *CTA* computed tomography angiography, *CTP* computed tomography perfusion, *DSA* digital subtraction angiography, *DWI* diffusion-weighted imaging, *MRA* magnetic resonance angiography, *MRI* magnetic resonance imaging, *mRS* modified Rankin scale, *NIHSS* National Institutes of Health Stroke Scale

### Outcome events and study measures

The primary outcome events will be defined as all strokes or deaths occurring between randomisation and the 30-day postoperative time point (for the nonsurgical group, this will be defined as all strokes or deaths occurring within 30 days post randomisation) and ipsilateral ischaemic stroke within 2 years post randomisation. A stroke is defined as rapid loss of neurological function due to ischaemia or a haemorrhage. Ipsilateral ischaemic stroke is further defined as the clinical diagnosis of a focal neurological deficit due to cerebral ischaemia that is clinically localisable within the territory of the symptomatic occluded ICA or MCA and that lasts for more than 24 h. CT or MRI scanning is necessary to identify the stroke.

Secondary outcome events include all strokes, disabling or fatal strokes and deaths between 30 days and 2 years post randomisation; severe TIA; complications associated with the surgical procedures; mRS score, National Institutes of Health Stroke Scale score (NIHSS) and Barthel Index assessment within 2 years; and anastomosis patency and haemodynamic changes within 2 years.

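### The stroke definition behind the 30-day part of the primary outcome has no minimum duration, while the later part requires more than 24 h; late strokes that kill quickly or before a scan can drop out of the primary outcome

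*Protocol article*

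**What the plan says.** All the relevant text but one sentence is in the protocol article under Outcome events and study measures.

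- Early component of the primary outcome: "all strokes or deaths occurring between randomisation and the 30-day postoperative time point". For the nonsurgical group the window is 30 days from randomisation.
- Late component: "ipsilateral ischaemic stroke within 2 years post randomisation". Death after the 30-day window is not a primary event.
- General definition: "A stroke is defined as rapid loss of neurological function due to ischaemia or a haemorrhage".
- Ipsilateral ischaemic stroke is then defined further as a focal ischaemic deficit "clinically localisable within the territory of the symptomatic occluded ICA or MCA and that lasts for more than 24 h".
- Imaging: "CT or MRI scanning is necessary to identify the stroke".
- Secondary outcomes: "Secondary outcome events include all strokes, disabling or fatal strokes and deaths between 30 days and 2 years post randomisation; severe TIA".

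The section Intervention and follow-up adds: "If a stroke is suspected, MRI or CT will be performed as soon as possible". The section Sample size and randomisation states that patients, clinicians and investigators all know the treatment assignment.

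**The concern.** The two components of one primary endpoint use different duration criteria. The stricter one applies only to the component that runs to 2 years. The looser one applies in the window that contains the operation. In an open-label trial, an assessor facing a deficit that clears within hours could call it a stroke under the general definition, or a TIA because TIA is listed elsewhere. The text supports either choice, and the choice could differ by arm, in either direction.

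The late component has the opposite gap. Its duration limit and the imaging sentence, taken literally, can exclude the most severe events: a stroke that kills within a day, or before a scan is obtained. Death itself is not a primary event at that stage, so nothing else in the primary outcome picks them up.

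What is at stake is whether primary events are classified the same way in both arms and in both periods.

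**Working it through.** **Step 1. Apply the written rules to specific events.**

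| Event | Within the 30-day window | After the window |
|---|---|---|
| Ischaemic deficit in the occluded territory, resolved in 2 h, scanned | Fits the general definition; can be primary | Fails the 24 h limit; not primary |
| Same deficit lasting 3 days, scanned | Primary | Primary |
| Ipsilateral ischaemic stroke, death within 24 h | Primary, as a death | Can fail the 24 h limit; counted as a secondary death |
| Ipsilateral ischaemic stroke, death before any scan | Primary, as a death | Can fail the imaging sentence; counted as a secondary death |

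The first row differs between periods only because "and that lasts for more than 24 h" belongs to one definition and not the other. The last two rows differ because death leaves the primary outcome after the window.

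**Step 2. Does the imaging sentence close the first gap?** It does not. It requires a scan but not a new lesion on it. Table 1 schedules brain CT/MRI at 7 and 30 days in both arms, so an early scan will usually exist. Patients enter after a qualifying TIA or ischaemic stroke within the past 12 months, so a scan may already show an old infarct. The sentence also does not say whether it covers every stroke or only ipsilateral ischaemic stroke.

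**Step 3. Are the windows alike?** Surgery takes place within 7 days of randomisation, so the surgical window can run to 7 + 30 = 37 days, against 30 in the nonsurgical group. The looser definition can therefore apply slightly longer in the surgical arm.

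**Step 4. Reproduce the plan's sample size.** Inputs from Sample size and randomisation: 28% and 14%, two-sided 5%, power 80%, 20% loss. With p̄ = (0.28 + 0.14)/2 = 0.21 and the pooled formula without continuity correction:

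n = [1.96·√(2·0.21·0.79) + 0.8416·√(0.28·0.72 + 0.14·0.86)]² / 0.14² = (1.129 + 0.478)² / 0.0196 ≈ 131.7, so 132 per group and 264 in total. Then 264/(1 − 0.20) = 330. Both stated figures reproduce, and the sample size arithmetic is not in question.

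**Step 5. Illustrate sensitivity.** Power = Φ{[|p₁ − p₂|·√n − 1.96·√(2p̄(1 − p̄))] / √(p₁(1 − p₁) + p₂(1 − p₂))}, with n = 132. The shifts below are assumptions; the document gives no rate of transient deficits or of unscanned fatal strokes.

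| Assumed shift | Control | Surgical | Power |
|---|---|---|---|
| None | 28% | 14% | 80.1% |
| +1 point, surgical only | 28% | 15% | 73.2% |
| +2 points, surgical only | 28% | 16% | 65.5% |
| +3 points, surgical only | 28% | 17% | 57.2% |
| +5 points, surgical only | 28% | 19% | 40.6% |
| +2 points in both arms | 30% | 16% | 77.4% |
| Late fatal strokes lost: −1 control, −0.5 surgical | 27% | 13.5% | 78.2% |
| Late fatal strokes lost: −2 control, −1 surgical | 26% | 13% | 76.3% |
| Late fatal strokes lost: −3 control, −1.5 surgical | 25% | 12.5% | 74.2% |

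On these assumptions, asymmetry between arms does most of the damage. An equal shift costs little.

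**The case against.** The strongest reply is that the article plainly distinguishes TIA from stroke. The inclusion criteria name them as alternatives, and severe TIA is a separate secondary outcome. A reader might infer that the protocol makes TIAs primary events by rule in the first 30 days. It does not say that, and the separate listing shows it was not meant. What stands is that no criterion in the text separates the two in that window, and the only stated definition admits a brief deficit.

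A reader might also infer that a late fatal stroke without a scan is counted nowhere. That is wrong: deaths between 30 days and 2 years are a secondary outcome, whether or not a scan was done. What remains is possible loss from the primary outcome, and from the secondary fatal strokes if the imaging sentence covers every stroke. Prompt examination and scanning of suspected events reduce the number but cannot help a patient who dies first.

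Third, nothing in the document shows that transient deficits occur mainly after surgery. NIHSS, mRS and brain imaging are scheduled alike in both arms at 7 and 30 days; only DSA, CTP and laboratory tests at 7 days are for surgical patients alone. So the surgical-only rows of the power table are possibilities, not estimates, and a claim that surgical events are inflated would go too far.

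Finally, how deaths without imaging are adjudicated is detail that an article may leave to the full protocol. That is fair as far as omission goes. The point here rests on the definitions that the article does state, which conflict between the two components.

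**Conclusion.** The point holds as an inconsistency in the stated primary endpoint. The general stroke definition lets a transient ischaemic deficit qualify in the first 30 days, when the same deficit would not qualify later. The 24 h limit and the imaging sentence can remove a rapidly fatal or unscanned late ipsilateral ischaemic stroke from the primary outcome, though not from the secondary deaths. Open-label assessment means that the ambiguity could be resolved differently by arm.

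Its size cannot be estimated from the document. Under assumed surgical-arm excesses of 1 to 5 points, with 132 per group and 28% in control, power falls from 80% to between 73% and 41%. With 2 extra points in both arms it is about 77%. These figures show sensitivity only. The change is worth making because it prevents arm-dependent classification at almost no cost.

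**What to change.** Use one stroke definition in both components: a neurological deficit due to ischaemia or haemorrhage that lasts more than 24 h or leads to death, with CT or MRI where obtainable. The late component keeps its restriction to ipsilateral ischaemic events. Count shorter episodes only as TIA, whenever they occur.

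Allow a fatal event without imaging to be classified as ipsilateral ischaemic stroke when the available clinical or autopsy evidence supports it. There should be no default assignment: calling every unscanned death ipsilateral ischaemic would bring haemorrhagic and contralateral deaths into a component that excludes them.

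The cost is a change of endpoint wording and a few events classified without imaging. The sample size need not change on this account.

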For the sample size calculation, we consulted the figures for stroke risk from MCA occlusion, which is different from ICA occlusion. In 1996, Yamauchi et al. [17] investigated patients with symptomatic ICA or MCA occlusive diseases. They found that the incidence of ipsilateral ischaemic strokes in patients with increased OEF and normal OEF was 57.1% and 6.0%, respectively. (They also suggested that patients with increased OEF had decreased CBF and CBF/CBV values.) Kuroda et al. [19] reported that the annual risks of total and ipsilateral stroke in patients with ICA or MCA occlusion and decreased rCBF and relative cerebral vasoreactivity (rCVR) were 35.6% and 23.7%, respectively. Actually, the total annual risk of ipsilateral stroke in patients with decreased rCBF only was 26.1%. In 2002, Ogasawara et al. [18] presented a study to prospectively evaluate the relationships between cerebral haemodynamics and outcome of patients with symptomatic major cerebral artery occlusion (including ICA and MCA) by quantitative measurement of CBF using ^133^Xe and single photon emission tomography (SPECT). During the follow-up, the recurrence rate of stroke was 34.7% in patients with reduced rCVR at entry and less than 6% in patients with normal rCVR. All these data indicate that the annual risk of stroke is relatively higher in MCA than in ICA occlusion. Recently, aggressive medical management has been more widely used, and according to the results of a follow-up by our centre over the last 3 years, the risk of stroke in ICA or MCA occlusion is about 28%, which conforms to the data mentioned. Compared with the medical treatment group (28%), a further 50% reduction in the surgical treatment group is considered to be clinically significant; that is 14%. Regarding perioperative morbidity, in the COSS [20] the perioperative rate for ipsilateral ischemic stroke was 14.4%, while the rate for the primary end point was 21.0%. This indicates that the stroke rate between 30 days to 2 years was about 7%. In the CMOSS, we have much stricter licensing of neurosurgeons; attending neurosurgeons are certified by their roles as chief surgeon in at least 15 consecutive previous EC-IC bypass surgeries. Using this level of expertise means that in China we can achieve an anastomosis graft patency rate of greater than 95% and a perioperative stroke and death rate of less than 10%.

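### Secondary stroke and death outcomes that start 30 days after randomisation leave out most of the perioperative period, and no listed outcome counts these events from randomisation to 2 years

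*Protocol article*

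**What the plan says.** The point rests on the protocol article's section on outcome events and study measures, read with the section on intervention and follow-up.

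- **Secondary events:** "Secondary outcome events include all strokes, disabling or fatal strokes and deaths between 30 days and 2 years post randomisation".
- **Other secondary outcomes that can reflect early harm:** "complications associated with the surgical procedures; mRS score, National Institutes of Health Stroke Scale score (NIHSS) and Barthel Index assessment within 2 years".
- **Primary outcome, early part:** in the surgical arm, "all strokes or deaths occurring between randomisation and the 30-day postoperative time point"; in the medical arm, "all strokes or deaths occurring within 30 days post randomisation".
- **Primary outcome, late part:** "ipsilateral ischaemic stroke within 2 years post randomisation".
- **Timing of the operation:** "Surgical intervention will be performed within 7 days after randomisation".

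The rationale section shows where surgical events are expected to cluster. Of the earlier bypass trial (COSS) it says that "the perioperative rate for ipsilateral ischemic stroke was 14.4%, while the rate for the primary end point was 21.0" per cent, and it puts the later stroke rate at about 7%. For the present trial it gives a perioperative stroke and death rate below 10%.

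**The concern.** The trial compares an operation that carries an early risk with medical treatment that does not. A count that opens 30 days after randomisation removes early events from both arms, but more of them from the surgical arm if the operation causes strokes or deaths. The late benefit then appears without the early cost.

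The primary outcome does not fill the gap. It is broad early (all strokes and deaths) and narrow late (ipsilateral ischaemic stroke only). The secondary events are broad, but only late. On the natural reading, no listed event outcome answers three ordinary questions for a patient deciding at randomisation: the 2-year risk of any stroke, of disabling or fatal stroke, and of death. The trial could then report favourable secondary results on stroke and death that do not describe the whole 2 years.

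**Working it through.** **1. What the window leaves out.** Let surgery take place on day s after randomisation, with s from 0 to 7. The secondary window opens on day 30, which is postoperative day 30 − s, so the first 23 to 30 postoperative days are excluded. The primary outcome's early window in the surgical arm closes on day 30 + s, at the latest day 37. Events from day 30 to day 37 in patients operated on late can therefore count in both windows.

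**2. The plan's own figure.** Inputs from the sample size section: 28% medical, 14% surgical, two-sided 5%, 80% power, 20% loss. With the pooled-variance formula and mean rate 0.21:

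n = [1.96 × √(2 × 0.21 × 0.79) + 0.842 × √(0.28 × 0.72 + 0.14 × 0.86)]² / 0.14² = 131.7, so 132 per group and 264 in total. 264 / 0.80 = 330. The stated size is reproduced, and this point does not affect it.

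**3. Share of surgical-arm events before the window opens.** In the earlier trial, 14.4 / 21.0 = 69%, leaving 21.0 − 14.4 = 6.6 points later. In this trial the perioperative rate is only bounded (below 10%), so I show a range against the planned 14%.

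**4. Relative risk (RR) after day 30.** With all randomised patients in the denominator:

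RR = (surgical 2-year rate − surgical 30-day rate) / (medical 2-year rate − medical 30-day rate)

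The document gives no medical 30-day rate. I assume a constant hazard: 1 − 0.72^(30/730) = 1.3%, which leaves 28 − 1.3 = 26.7%. The range shown is 0% to 5%. Perioperative events are treated as falling before day 30.

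| Surgical 30-day rate | Share of the 14% | Surgical, after day 30 | RR, medical 30-day 1.3% | RR, medical 0% to 5% |
|---|---|---|---|---|
| 3% | 21% | 11% | 11/26.7 = 0.41 | 0.39 to 0.48 |
| 5% | 36% | 9% | 9/26.7 = 0.34 | 0.32 to 0.39 |
| 7% | 50% | 7% | 7/26.7 = 0.26 | 0.25 to 0.30 |
| 10% (ceiling) | 71% | 4% | 4/26.7 = 0.15 | 0.14 to 0.17 |

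Counted from randomisation, the RR is 14/28 = 0.50 in every row.

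**5. No net effect.** Take 28% in both arms with 10% perioperative events. The window gives (28 − 10)/26.7 = 0.68 instead of 1.00. With a 5% medical 30-day rate it gives 18/23 = 0.78.

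**6. Direction.** On the risk-difference scale the window favours surgery exactly when early events are more frequent in the surgical arm. On the relative-risk scale it does so when the early RR exceeds the 2-year RR. The tilt is not automatic: with 28% in both arms, a 3% surgical and a 5% medical 30-day rate, the window reads (28 − 3)/(28 − 5) = 1.09, against bypass.

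**The case against.** The strongest reply is that the two outcome sets complement each other. The primary outcome takes all strokes and deaths early, and the secondary list adds the late strokes and deaths that the primary omits. Surgical complications are listed separately, and Table 1 schedules NIHSS, mRS, Barthel Index and adverse events at 7 and 30 days. This stands as far as it goes: a reader might infer that early surgical harm becomes invisible to the trial, and the document does not support that, because every early stroke or death is a primary event. It does not close the gap. The primary outcome does not separate disabling strokes from others or report death alone, surgical complications have no counterpart in the medical arm, and late counts added to early ones are not a patient-level 2-year outcome, all the more because the windows can overlap by up to 7 days.

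Other parts of the reply also stand:

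- **The wording is ambiguous.** The time limit might attach only to deaths. All-cause death would then still be truncated, and the stroke outcomes would have no stated start.
- **Loss of patients from the comparison.** A reader might infer that those with an early stroke or death drop out and so break the randomised comparison. No risk set is defined in the document, and such a rule commonly sits in an analysis plan. The calculation above keeps everyone in the denominator.
- **Days 30 to 37.** Late perioperative events inside the secondary window count against surgery and slightly offset the tilt.
- **The hypothesis.** The abstract speaks of testing whether "EC-IC bypass surgery plus best medical therapy reduces subsequent ipsilateral ischaemic stroke", without the early component. One might read a slant into this, but the same abstract gives the full primary outcome, and the sentence changes no analysis.

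**Conclusion.** The point holds for the secondary stroke and death outcomes only. On the natural reading their window omits nearly all of the perioperative period, and the comparison favours bypass if early events are more frequent after surgery, as the quoted experience of the earlier trial suggests. The primary outcome and the sample size are unaffected.

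The size is illustrative. The rates are those of the primary composite, because the document gives none for all stroke, disabling or fatal stroke, or death. The medical 30-day rate is an assumption. A reader might take 0.15 as the expected result, but it sits at the 10% ceiling, which the document states as an upper bound. At 3% the distortion is modest (0.41 instead of 0.50). The clearest case is that of no net effect with 10% perioperative events, where a treatment without benefit would read 0.68, or 0.78 with a 5% medical 30-day rate.

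**What to change.** Define any stroke, disabling or fatal stroke, and all-cause death each from randomisation to 2 years, in all randomised patients by assigned group. Keep the counts from 30 days to 2 years only as a supportive landmark, labelled as such and shown beside the early-period counts for both arms. State to which events the time limit applies and how days 30 to 37 are assigned in patients operated on late, so that the two periods join without overlap.

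This is a change of wording. The early strokes and deaths are already needed for the primary outcome and the late ones for the present secondary list, so no new visits or data are required. The cost is that the surgical arm's secondary results will look less favourable. The article reports that recruitment is continuing and that treatment assignment is open, so the change should be made before outcomes are compared by arm.
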